### Randomization and Allocation

2.5

The permuted block randomization method will be employed using a web‐based computer software, in which patients will be allocated into two groups (SCRT and LCRT) with random block sizes of four. Allocation will be done according to the generated numbers and the time of enrollment.

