## Methods/Design

2

Patients with locally advanced rectal adenocarcinoma (T3 or T4 primary tumor and/or lymph node‐positive disease), who are referred to the Cancer Institute of Imam Khomeini Hospital Complex, Tehran, from September 2023 to the end of March 2025, will participate in this phase 3, randomized, investigator‐blinded, parallel group study. The initial workup comprises total colonoscopy, contrast‐enhanced thoracoabdominopelvic computed tomography (CT) scan, pelvic magnetic resonance imaging (MRI) with intravenous gadolinium, and routine blood tests including tumor markers (carcinoembryonic antigen [CEA] and cancer antigen [CA] 19–9), complete blood count, as well as liver and renal function tests. An expert radiologist will be assigned to review the MRI images and determine the caudal tumor distance from the anal verge, exact T and N staging per the American Joint Committee on Cancer (AJCC) eighth edition, intactness of the mesorectal fascia, circumferential radial margin (CRM), the exact number, location, and the largest size of the pathologic lymph nodes, presence of extramesorectal lymphadenopathies, and extramural vascular invasion (EMVI). For patients who have a high CEA above 20 ng/mL, a positron emission tomography will be requested to rule out distant metastasis. The mismatch repair (MMR) system will be evaluated by immunohistochemistry on the biopsy specimen for all patients before randomization. Informed consent will be obtained from patients after a thorough explanation of the treatment process; if a patient decides to withdraw from the study, they will be removed and receive the standard protocol treatment. The study protocol was approved by the Research Ethics Committees of Imam Khomeini Hospital Complex–Tehran University of Medical Sciences (TUMS) (approval number: IR.TUMS.IKHC.REC.1401.238).

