### Blinding

2.6

Blinding will only be applied at the level of treatment response assessment by a radiologist who will be blinded to the treatment groups, as well as the researcher in charge of data analysis. The treatment nature does not allow blinding of the patients and the physicians in charge of treatment.

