### Sample Size Calculation

2.7

Considering a predicted cCR rate of 76% as reported in the OPRA trial [18] for the LCRT plus consolidation chemotherapy group, and a cCR rate of 52% in the SCRT plus consolidation chemotherapy as reported by a retrospective study [19], to achieve a 90% power with a two‐sided type I error of 5%, we will require 79 patients in each arm [20]. To compensate for an estimated dropout rate of 20%, we will recruit 95 patients to each study group.

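### A single block size of four is called random; in this open-label, one-centre trial, staff who know the size and track allocations could foresee about a third of assignments

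*Protocol article*

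**What the plan says.** Section 2.5 (Randomization and Allocation) states that "The permuted block randomization method will be employed" through web-based software, for two groups, "with random block sizes of four". It adds: "Allocation will be done according to the generated numbers and the time of enrollment". No stratification factor is named. The 1:1 ratio is not stated outright but follows from the equal group sizes in section 2.7.

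Section 2.6 (Blinding) limits blinding to the radiologist who assesses response and the data analyst, and says: "The treatment nature does not allow blinding of the patients and the physicians in charge of treatment".

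Section 2 (Methods/Design) describes the population as patients "who are referred to the Cancer Institute of Imam Khomeini Hospital Complex, Tehran". No other recruiting centre is mentioned.

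**The concern.** The phrase in section 2.5 contradicts itself. Random block sizes means that the size varies, but only one size is given. Either the order within fixed blocks of four is random, or the size varies and the number four is wrong.

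On the first reading, the design makes the sequence open to deduction. In a 1:1 block of four, once two patients have gone to one arm, the rest of the block is known. Treatment is visible (5 fractions against 28), there is one centre, and no strata are stated that would split the sequence into separate lists. The block size is printed in the article.

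Someone who expects a particular arm next could hold back or delay a patient. The document shows why opinions might differ between arms. Its Discussion reports warnings about short-course treatment in patients with high-risk local features, and section 2.7 assumes a complete clinical response of 76% with long-course against 52% with short-course treatment. Selection of this kind would make the arms differ at entry. A blinded MRI reading does not repair that. Nor does the chi-squared test in section 2.9, and the logistic regression planned there could adjust only for recorded features.

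**Working it through.** **Inputs.** Block size 4 (section 2.5); two arms, 1:1 implied by 79 or 95 per arm (section 2.7). The total is 2 × 79 = 158, also the number given in the Abstract, or 2 × 95 = 190 with the dropout allowance. The plan states no predictability figure to reproduce. Its 79 per arm is reproduced by the unpooled two-proportion formula (78.8, rounded up) and is not affected by this point.

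**Certain predictions, fixed blocks of four.** The six equally likely orders are AABB, BBAA, ABAB, ABBA, BAAB and BABA. In the first two, the last two positions are forced. In the other four, only the last position is forced.
- Expected forced positions per block: (2 × 2 + 4 × 1)/6 = 8/6 = 1.333.
- Share: 1.333/4 = 33.3%.
- For 190 patients: 47 full blocks plus 2 patients. The first two positions of a block are never forced, so 47 × 4/3 = 62.7, about 63.
- For 158 patients: 39 full blocks plus 2 patients, so 39 × 4/3 = 52.

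**Best guess, fixed blocks of four.** The observer guesses the arm less used so far in the block.
- Position 1: 1/2.
- Position 2: 2/3.
- Position 3: 1/3 × 1 + 2/3 × 1/2 = 2/3.
- Position 4: 1.
- Sum 17/6 = 2.833 of 4, or 70.8%.

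**Alternatives.** Fixed blocks were enumerated. Mixed blocks were simulated (1,000 trials of 190 patients, sizes equally likely) against an observer who knows the set of sizes and every earlier allocation, but not the size of the current block.

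| Scheme | Known with certainty | Best guess correct |
|---|---|---|
| Fixed 4 | 33.3% | 70.8% |
| Fixed 6 | 25.0% | 68.3% |
| Fixed 8 | 20.0% | 66.6% |
| Random 4/6 | about 5.5% | about 69% |
| Random 4/6/8 | about 2.2% | about 68% |

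**Illustration of scale (an assumption, not a figure from the document).** Suppose steering moves the response probability of enrolled patients by ±5 points according to the arm expected.
- Acting on every best guess with blocks of four creates a spurious difference of 2 × 5 × (2 × 0.708 − 1) = 4.2 points. At ±10 points it is 8.3.
- Acting only on certain predictions gives 2 × 5 × 0.333 = 3.3 points. At ±10 points it is 6.7.
- Under random 4/6/8, and still at ±5 points, these become 2 × 5 × (2 × 0.68 − 1) = 3.6 and 2 × 5 × 0.022 = 0.2.

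The change therefore nearly removes steering on certainty, but not steering on guesses by someone who knows the sizes.

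**The case against.** Four things can be said for the plan.

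1. **The one-third figure is conditional.** It needs an observer who knows the block size, knows where each block starts and has followed all earlier allocations in order. This stands. A reader might infer that the treating physicians also recruit and see every allocation. The document says only that they are not blinded; it does not say who enrols patients, who operates the software, or whether anyone sees the whole sequence. With one centre and a published block size such knowledge is plausible, but it is not established.

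2. **The web-based system conceals the list.** It may, and a condensed article can leave release of allocations and other concealment steps to the full protocol, so their absence is no fault here. A reader might infer from the sentence on time of enrolment that nothing is concealed, but that sentence only gives the order of allocation. Concealing the list, however, does not prevent deduction from past open-label allocations.

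3. **The phrase may be a slip for varying sizes.** That is possible. The 33% would then not apply, and only the sentence would need correcting.

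4. **Varying sizes barely change the best guess.** This is right for an observer who knows the set of sizes: about 71% becomes about 68%. The gain lies in certain prediction, and keeping the sizes from recruiting staff makes guessing harder still.

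**Conclusion.** The point holds as an internal contradiction plus a conditional design weakness. The wording in section 2.5 must change on either reading. If blocks are fixed at four and allocation is 1:1 without strata, 33% of assignments (about 63 of 190, or 52 of 158) are predictable with certainty, and 71% can be guessed correctly, by staff who know the size and track the sequence.

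A reader might go further and conclude that the comparison is biased. The document does not support that: it shows exposure, it contains no evidence of steering, and fixed blocks of four remain a valid 1:1 scheme. The change is worth making because it is cheap and removes nearly all certain prediction. It does not remove the guessing advantage.

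**What to change.** Rewrite the sentence in section 2.5 to say that allocation is 1:1 in permuted blocks whose size varies at random, for example among 4, 6 and 8, and that the sizes are not disclosed to recruiting staff. If varying sizes were already in use, only the wording needs correcting.

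The recruitment periods given in section 2 (to the end of March 2025) and section 2.8 (to 22 September 2025) suggest that many patients may already be randomised. If fixed blocks of four were used, correct the wording, disclose this in the report and use varying sizes for any remaining patients. Also compare baseline cT, cN and CEA by position in block. The most telling contrast is between arms among the forced allocations, which should look alike if nobody steered. With about 31 such patients per arm (63/2), a reassuring result would be weak evidence.

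The cost is a software setting, one sentence and one baseline table. The possible final imbalance rises from at most 2 patients (half a block of four) to at most 4 (half a block of eight), which is negligible against 158 or 190. The sample size does not change.

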### Blinding

2.6

Blinding will only be applied at the level of treatment response assessment by a radiologist who will be blinded to the treatment groups, as well as the researcher in charge of data analysis. The treatment nature does not allow blinding of the patients and the physicians in charge of treatment.

### Sample Size Calculation

2.7

Considering a predicted cCR rate of 76% as reported in the OPRA trial [18] for the LCRT plus consolidation chemotherapy group, and a cCR rate of 52% in the SCRT plus consolidation chemotherapy as reported by a retrospective study [19], to achieve a 90% power with a two‐sided type I error of 5%, we will require 79 patients in each arm [20]. To compensate for an estimated dropout rate of 20%, we will recruit 95 patients to each study group.

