### Statistical Analysis

2.9

Basic descriptive tests will be used for qualitative data. Normality will be tested for the quantitative data using the Kolmogorov–Smirnov test. To compare the qualitative data, Pearson's chi‐squared test, and for the comparison of quantitative data, an independent samples t‐test will be used. A binary logistic regression analysis will be performed to determine the predictors of cCR. All analyses will be done in the intention‐to‐treat population. We will also perform subgroup analysis on patients with a cCR who choose a watch‐and‐wait approach after TNT to determine predictors of survival outcomes. Analyses will be done using IBM SPSS Statistics version 26 with a *p* value of 0.05 as the significance boundary.

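### Recruiting 95 per arm does not cover the stated 20% dropout: it leaves 76 evaluable patients per arm, not the 79 required, and costs about 1.2 points of power

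*Protocol article*

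**What the plan says.** Section 2.7 (Sample Size Calculation) assumes a complete clinical response (cCR) rate of 76% with long-course treatment and "a cCR rate of 52% in the SCRT plus consolidation chemotherapy" group. With a two-sided type I error of 5%, and "to achieve a 90% power", it arrives at 79 patients per arm. It then adds the allowance for loss: "To compensate for an estimated dropout rate of 20%, we will recruit 95 patients to each study group". The inflation formula is not shown.

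Two other places bear on this. Section 2.9 (Statistical Analysis) names Pearson's chi-squared test for qualitative data and states: "All analyses will be done in the intention‐to‐treat population". It does not say how a patient without a response assessment counts for cCR. The Methods paragraph of the abstract gives the number to be randomized as 158.

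**The concern.** A dropout rate is a share of those recruited, so the number recruited has to be the required number divided by the share retained. Multiplying the required number by one plus the dropout rate always falls short, and 95 is what that multiplication gives. On the plan's own figures, the recruited number therefore does not leave the 79 per arm on which the 90% power rests. That power will be cited if the trial shows no difference between the arms, so it should be a property of the design as stated.

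A related question is what the allowance is for. Inflating for dropout presumes that patients who are lost leave the primary comparison, while an intention-to-treat analysis keeps them in. The power then depends on how they are counted.

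**Working it through.** **Inputs.** From section 2.7: cCR 0.76 and 0.52, two-sided 5% (z = 1.960), power 90% (z = 1.2816), equal arms, 79 required, 20% dropout, 95 recruited. From section 2.9: Pearson's chi-squared test and the intention-to-treat population.

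**Step 1: reproduce 79.** The unpooled two-proportion formula is

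n = (1.960 + 1.2816)² × (0.76 × 0.24 + 0.52 × 0.48) / (0.76 − 0.52)²
= (1.960 + 1.2816)² × (0.1824 + 0.2496) / 0.24² = 78.8, rounded up to 79.

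The plan's figure reproduces. The pooled formula gives 82.

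**Step 2: the inflation.**

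- 79 × 1.20 = 94.8, rounded up to 95: matches the plan.
- 79 / (1 − 0.20) = 98.75, rounded up to 99: does not match.
- Retained from 95: 95 × 0.80 = 76. Retained from 99: 99 × 0.80 = 79.2.
- Dropout that 95 does cover: 1 − 79/95 = 16.8%.

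**Step 3: power at 79 and at 76 per arm (76% vs 52%).** For the unpooled formula, power is Φ(0.24 / √(0.432/n) − 1.960), where 0.432 = 0.1824 + 0.2496. At n = 76 this is Φ(3.183 − 1.960) = Φ(1.223) = 88.9%.

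| Method | 79 per arm | 76 per arm |
|---|---|---|
| Unpooled (the formula that yields 79) | 90.1% | 88.9% |
| Pooled | 88.9% | 87.7% |
| Exact enumeration of the chi-squared test | 89.3% | 88.1% |

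Each row falls by about 1.2 points. That fall is the effect of the inflation error. The pooled and exact rows already lie below 90% at the full 79, and that part of the gap comes from the choice of formula, not from dropout.

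**Step 4: range under intention-to-treat at 95 per arm.** The counting rule is not in the document, so both ends are assumptions.

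- *All 20% counted as not cCR in both arms:* the rates become 0.8 × 0.76 = 60.8% and 0.8 × 0.52 = 41.6%. Power is 77.0% unpooled, 75.8% pooled and 75.9% exact. At 99 per arm the pooled figure is still only 77.5%.
- *All 95 assessed, with the assumed rates holding:* power is 94.5% unpooled, 93.8% pooled and 93.9% exact.

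**Step 5: the total.** 2 × 79 = 158, 2 × 95 = 190 and 2 × 99 = 198. The abstract's 158 is the total with no allowance for dropout.

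**The case against.** The strongest reply is that this hardly matters. The gap is three evaluable patients per arm, the 20% is itself an estimate, and 95 per arm is still enough if dropout stays at or below 16.8%. That stands, and it limits the size of the point. It does not make the sentence right, because it claims to compensate for 20%.

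It can also be said that the route to 95 is inferred, since no formula is printed. This is true, but the shortfall does not depend on the route: 80% of 95 is 76 however 95 was reached.

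A reader might go further and infer that the trial's real power is about 76%. The document does not support that. The figure needs a rule that unassessed patients count as not cCR, and section 2.9 states no such rule. A journal article may leave that detail to a fuller document, so its absence is not a fault in itself. Nor does section 2.7 define dropout. If patients who stop treatment are still assessed, power at 95 per arm could be about 94%. Moreover, correcting 95 to 99 would not repair the low scenario, so that scenario cannot be charged to the inflation error.

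A reader might likewise set 87.7% or 88.1% against the stated 90% and blame the whole gap on the inflation. The 79-per-arm column shows that about half of it would be there anyway.

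**Conclusion.** The point holds as a small, definite arithmetic error. On the plan's own 20%, 95 per arm leaves 76 and not 79. The loss of power is about 1.2 points whichever formula is used, from 90.1% to 88.9% by the formula behind the 79. This rests on the plan's assumed response rates and on dropouts leaving the primary comparison, which is what an inflation for dropout implies.

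Under intention-to-treat, all that can be said is that power at 95 per arm depends on a rule the article does not state, within a range of about 76% to 94%. Neither end is a property of the plan as written. The error does not make the trial materially underpowered, but it does make the stated 90% unsupported by the stated recruitment, and it should be corrected.

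**What to change.** In section 2.7, do one of the following:

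- Keep 95 per arm and restate the power as about 88–89% with 76 evaluable per arm. This costs one sentence and a slightly less favourable figure.
- Correct the target to 79 / 0.80 = 99 per arm, 198 in total. This costs 8 more patients than the present 190.

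In either case, say how patients without a response assessment count for cCR in the intention-to-treat analysis, and give the power under that rule. If the rule is still open and 95 is kept, give the range with its assumptions: about 76–77% if all 20% count as not cCR, up to about 94% if all 95 are assessed.

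Change the 158 in the abstract to agree with the total chosen: 190 if 95 per arm is kept, 198 if the target becomes 99. Apart from the 8 patients in the second option, these are wording changes only.

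### The 20% dropout allowance is too small: 95 recruits per arm leave 76, not the required 79, so the stated 90% power is not met

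*Protocol article*

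**What the plan says.** Section 2.7 of the protocol article builds the sample size in two steps.

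- **Requirement.** The inputs are complete clinical response rates of 76% with long-course treatment ("Considering a predicted cCR rate of 76% as reported in the OPRA trial") and 52% with short-course treatment ("a cCR rate of 52% in the SCRT plus consolidation chemotherapy"), a two-sided 5% level, and a sample large enough "to achieve a 90% power". The result is: "we will require 79 patients in each arm".
- **Allowance for dropout.** "To compensate for an estimated dropout rate of 20%, we will recruit 95 patients to each study group". The section does not show how 95 was obtained from 79.

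Two other sections bear on how dropouts enter the analysis. Section 2 (Methods/Design) says that patients who withdraw are removed from the study. Section 2.9 (Statistical Analysis) puts all analyses on an intention-to-treat footing and names Pearson's chi-squared test for categorical data.

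**The concern.** If a fraction d of recruited patients is lost, the number to recruit is the required number divided by (1 − d). Multiplying by (1 + d) always gives too few, because the loss falls on the larger recruited number and not on the required number. The stated 95 matches the second calculation and not the first.

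The recruitment target and the power are figures on which readers, the ethics committee and the eventual trial report will rely. As written, 79 evaluable, 20% dropout and 95 recruited cannot all hold, so the trial would be reported with a power that its own assumptions do not give.

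**Working it through.** **Inputs.** Response rates p1 = 0.76 and p2 = 0.52, two-sided 5% level (z = 1.960), 90% power (z = 1.2816), 20% dropout, 79 required and 95 recruited per arm, all from section 2.7. Section 2.5 describes two groups ("patients will be allocated into two groups (SCRT and LCRT) with random block sizes of four"), and section 2.7 gives them equal sizes. The test is from section 2.9.

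**1. Reproduce the plan's 79.** With the unpooled variance,

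n = (z₁ + z₂)² × [p1(1 − p1) + p2(1 − p2)] / (p1 − p2)²

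= (1.960 + 1.2816)² × (0.1824 + 0.2496) / 0.24² = 78.8, rounded up to 79.

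This matches. So 79 is the evaluable number before any allowance, with no hidden margin. (The formula that pools the variance under the null gives 82, and a continuity correction gives 91.)

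**2. Reproduce the plan's 95.**

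- 79 × (1 + 0.20) = 94.8, rounded up to 95: matches.
- 79 / (1 − 0.20) = 98.75, rounded up to 99: does not match.

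The multiplication by 1.2 is inferred from the match. The next step does not depend on that inference.

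**3. Apply the stated dropout to the stated recruitment.**

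- 95 × 0.80 = 76 evaluable per arm, 3 short of 79.
- The largest loss that still leaves 79 is (95 − 79)/95 = 16/95 = 16.8%.
- The recruitment shortfall is 99 − 95 = 4 per arm, or 198 − 190 = 8 in total.

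**4. Power at 76 and at 79 per arm.** For the unpooled formula, power = Φ(0.24/√(0.4320/n) − 1.960):

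- n = 76: √(0.4320/76) = 0.0754, 0.24/0.0754 − 1.960 = 1.223, power 88.9%.
- n = 79: √(0.4320/79) = 0.0739, 0.24/0.0739 − 1.960 = 1.286, power 90.1%.

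The same comparison by three methods:

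| Method | 79 per arm | 76 per arm | Loss (points) |
|---|---|---|---|
| Unpooled formula (gives the plan's 79) | 90.1% | 88.9% | 1.1 |
| Pooled formula | 88.9% | 87.7% | 1.2 |
| Exact enumeration, uncorrected Pearson chi-squared | 89.3% | 88.1% | 1.2 |

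Losses are taken from the unrounded values. Power at 76 per arm is below 90% by every method. By the exact Pearson calculation the gap to 90% is 1.9 points. Of these, 1.2 come from the dropout step and 0.7 from the formula used to obtain 79.

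**5. Sensitivity to how dropouts are counted.**

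- All 95 per arm analysed at unchanged rates: 94.5% (unpooled formula) or 93.9% (exact Pearson).
- Dropouts kept and counted as non-responders: the rates become 0.76 × 0.8 = 60.8% and 0.52 × 0.8 = 41.6%, and power by the pooled formula is about 76% at 95 per arm and about 78% at 99.

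**The case against.** The strongest reply is that the shortfall exists only if dropouts have no response outcome. Section 2.9 promises intention-to-treat analysis. If all 95 per arm were analysed at the assumed rates, power would be about 94%, above the stated figure. This does not rescue the sentence. An allowance for dropout has a purpose only if dropouts are lost to the primary analysis, and section 2 says that withdrawals are removed. If instead everyone yielded an outcome, no allowance would be needed. If dropouts were kept as non-responders, power would fall to about 76%.

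Three further points stand and limit the weight of the finding:

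- **The loss is small.** It is just over one point of power, and the 20% is itself a round estimate. By the plan's own formula, moving one assumed rate by one point (75% against 52%) raises the requirement from 79 to 87 and lowers power at 79 per arm to 87.1%.
- **Recruiting 99 restores the headcount, not 90% on every method.** It returns 79 evaluable, which is 90.1% by the plan's formula but 89.3% by the exact Pearson calculation. That calculation gives 90.3% at 83 per arm.
- **A larger conflict sits beside it.** The abstract gives 158 patients to be randomized, which is 2 × 79 with no allowance, against 2 × 95 = 190 in section 2.7. If 158 were the real target, 20% loss would leave about 63 per arm and about 83% power by the unpooled formula. Settling that in favour of 190 would still leave the error described here.

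**Conclusion.** The concern holds. At 20% dropout, recruiting 95 per arm leaves 76 evaluable patients and not 79. The recruitment consistent with section 2.7's own requirement is 99 per arm. Power at 76 per arm is 88.9% on the plan's formula and 88.1% by exact Pearson, against the stated 90%.

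This rests on the plan's own response rates and on dropouts contributing no primary outcome. It is a definite arithmetic error with a modest effect. It does not undermine the design, but a figure that readers will rely on is wrong and easily corrected.

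**What to change.** Change one sentence in section 2.7 in one of these ways:

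1. **Keep 95 per arm and restate the power.** With 20% dropout, 76 per arm remain, giving about 89% power by the formula used for the sample size, or about 88% by exact calculation for Pearson's chi-squared test. Name the method with the figure.
2. **Keep 95 per arm and 79 evaluable, and restate the allowance.** 95 per arm allows for about 17% dropout.
3. **Keep both 79 evaluable and 20% dropout.** The recruitment figure is then 99 per arm, 198 in total.

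The first two need no extra patients. The first makes the stated power 1 to 2 points less favourable. The third adds 8 patients. In the same edit, state whether dropouts leave the primary analysis or are counted as non-responders, so that the allowance agrees with the intention-to-treat statement in section 2.9, and bring the abstract's 158 into line with the chosen total.
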